The second objective is to examine whether effects of mindfulness and fantasizing on PC in rMDD individuals differ from ND individuals. To this end, 50 ND participants will be matched to the rMDD participants and similarly randomized to undergo both mindfulness and fantasizing interventions. Comparing the effects of interventions in both rMDD and ND individuals allows us to study whether therapeutic techniques, developed and often studied in a clinical sample, work similar or different in ND individuals. Since most studies focus on the effects of mindfulness and positive fantasizing in a clinical sample [16, 19, 27, 28, 42], we hypothesize these techniques to be effective in reducing PC in rMDD individuals but expect that the interventions may show different effects on PC in ND individuals.

The third objective is to examine in an exploratory manner whether individual characteristics affect the effectiveness of the two interventions in reducing PC across all participants (i.e., what works for whom). We know from the previous literature that there is substantial variability in treatment response between MDD individuals [43,44﻿]. This variability has been suggested to be related to individual characteristics such as depressive symptoms and history, comorbid disorders/symptoms, personality traits, and cognitive dysfunction. For example, people with anhedonia may have a harder time to engage in positive fantasizing, and people with lower levels of executive functioning (mental flexibility) may find mindfulness practice difficult. Whether these independent predictors of depressive vulnerability affect intervention effects is interesting for personalized treatment purposes. This objective is exploratory, and hence we do not have specific hypotheses about the direction of these effects.

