### Recruitment

Participants are recruited via advertisements campaigns on (social) media, posters, and flyers in public spaces and patient organizations. After inclusion of a rMDD participant, a ND control participant is matched based on their age, sex, and education level.

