### Interventions

#### Mindfulness

Mindfulness-Based Cognitive Therapy is an eight-week intervention, consisting of eight training sessions of around two hours and daily practice at home of 30–40 min [24]. The intervention aims at increasing mindfulness and/or decreasing negative repetitive thoughts, and has been shown to reduce depressive relapse rates, depressive symptoms, and rumination [23, 25, 26]. In this study, we isolate two important aspects of Mindfulness-Based Cognitive Therapy, namely the professional training and short daily exercises.

In the current study, participants receive one professional training session (2 h) in the intervention in groups of 2–8 people to become familiar with the techniques, learn the basics needed for the daily exercises, and get questions answered. The training is given by a mindfulness professional and consists of psycho-education, instructions for mindfulness, and guided practice. It focuses mainly on attending to stimuli such as breathing, external sounds or bodily sensations, and becoming aware of where one’s attention is. For practical reasons, we work with two mindfulness professionals that alternate the training sessions.

After the professional training, participants receive instructions about the audio application with which they continue performing short exercises using the learned technique every day guided by an application on their smartphone customized for this research. Specifically, participants perform one short exercise (10 min) per day for in total six days. The exercises that are being performed are:day 1: attention to breathing part 1;day 2: attention to breathing part 2;day 3: attention to sounds;day 4: attention to bodily sensations;day 5: attention to thoughts;day 6: attention to emotions and feelings.

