### Randomization

All participants receive both interventions, which intervention they receive first is pseudo-randomly counterbalanced across participants. Pseudo-randomization here means that individuals are randomized to either fantasizing or mindfulness as first intervention by order of inclusion. Specifically, every three weeks a new measurement session starts. Mindfulness and fantasizing alternate in three-week blocks. New sign-ups in this three-week block are allocated to mindfulness or fantasizing, in alternating order.

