To address the secondary objective about the role of sleep on the effectiveness of interventions in reducing PC, we will be using LMEs or GAMs depending whether the data are nonlinear. If sleep plays a role in whether interventions reduce PC, we expect to find a main effect of sleep (i.e., total sleep time, sleep quality and sleep onset latency) on changes in self-reported PC after the interventions.

To study the effects of the interventions on depressive symptoms using self-report questionnaires, a repeated measures ANOVA will be used with questionnaire scores (IDS-SR, PTQ, RPA, ERQ, FFMQ, LARSS, PANAS) administered as dependent variable and intervention (fantasizing or mindfulness) and session (pre- or peri-intervention) as independent variables. If interventions differentially affect depressive symptoms, we expect to find an interaction effect between intervention and session.

### Study aim 2

To study whether changes in PC by fantasizing and mindfulness are different in individuals with rMDD vs. ND controls, we will run the same analyses as for study aim 1, but with the variable group (rMDD or ND) added as an independent variable. Specifically, to examine the differential effects of self-reported PC, HR(V), and EEG, we will include session and intervention in interaction with group as independent variables in the model. If changes in PC after interventions are different in rMDD vs. ND individuals, we expect to find an interaction effect between group, session, and intervention on self-reported PC and its (neuro)physiological correlates measured with HR(V) and EEG.

### Study aim 3

For the third objective of exploring the role of individual characteristics on the effectiveness of the interventions at reducing PC, we will use baseline individual characteristics of participants assessed by means of a set of questionnaires (e.g., mindfulness, rumination, emotion regulation strategies, psychiatric history, personality, dysfunctional attitudes, childhood trauma etc.) and correlate those with changes in 1) self-reported measures of PC measured with ESM and the SART, 2) HR and HRV during reported PC, and 3) EEG characteristics during PC measured with the SART after mindfulness and positive fantasizing interventions. When significant correlations are found, we will do post-hoc moderation analyses to see how specific individual characteristics moderate changes in PC.

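### The order rule does not secure balance of first technique within rMDD and within ND, so a period effect on change can leak into the aim 2 interaction

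*Protocol article*

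**What the plan says.** The Randomization section of the protocol article states that "which intervention they receive first is pseudo-randomly counterbalanced across participants". It defines the method as follows: "Pseudo-randomization here means that individuals are randomized to either fantasizing or mindfulness as first intervention by order of inclusion". Two further sentences give the mechanics: "Mindfulness and fantasizing alternate in three-week blocks", and "New sign-ups in this three-week block are allocated to mindfulness or fantasizing, in alternating order". Neither names a group stratum.

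On entry to the study, the Recruitment section says: "After inclusion of a rMDD participant, a ND control participant is matched based on their age, sex, and education level". It gives no lag. The Background (second objective) adds that "50 ND participants will be matched to the rMDD participants and similarly randomized to undergo both mindfulness and fantasizing interventions", which does not say whether a matched pair shares an order.

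The aim 2 test is stated under Statistical analyses, Study aim 2: "we expect to find an interaction effect between group, session, and intervention on self-reported PC". The model terms listed there are group, session and intervention. The planned size is 50 per group, with 25 per group for EEG, ECG/ICG and actigraphy.

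**The concern.** The rule uses inclusion sequence, and the recruitment plan ties inclusion sequence to group, because a control comes after its match. Balance over all 100 participants is compatible with imbalance inside each group, and aim 2 compares the groups.

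The design protects against one kind of period effect. Each period has its own pre-intervention week, after a wash-out of at least one month, so a plain shift in level between periods cancels. It does not protect against a difference between periods in the pre-to-peri change itself, through practice, fatigue, novelty or carry-over. Such an effect is not far-fetched on the article's own reasoning. The exclusion criteria bar people with recent practice in either technique so that effects are not underestimated. By period 2 every participant has had a two-hour training and six daily exercises in the other technique. That is less exposure than the exclusion threshold for mindfulness, so it makes the mechanism plausible and says nothing of its size.

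At stake is the reading of aim 2: a difference in order mix could appear as a difference in how rMDD and ND respond to the two techniques.

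**Working it through.** The article gives no figure on order balance, so there is none to reproduce.

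**Inputs.** From the article: 50 per group (25 for physiology), critical p-value 0.05, alternation by inclusion, controls entering after their matches. Assumed, because the article gives no value: delta, the period 1 minus period 2 difference in pre-to-peri change, in SDs of the person-level mindfulness-minus-fantasizing difference (0.1 to 0.3 shown), and the entry lag of controls.

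**Bias.** For one person let d = change under mindfulness − change under fantasizing. Its mean is tau_g + delta if mindfulness comes first and tau_g − delta if it comes second. With share p_g starting with mindfulness, the group mean is tau_g + delta(2p_g − 1). Hence the rMDD − ND contrast is

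(tau_r − tau_n) + 2(p_r − p_n) × delta.

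The last term is the bias when no period term is fitted. It is 0 when p_r = p_n. If both shares are one half, it is 0 even when delta differs between the groups, since each (2p_g − 1) is 0.

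**Type I error at a fixed gap.** Two-sided t-test, SE = sqrt(2/n), noncentrality = 2 × gap × delta / sqrt(2/n). Example: gap 1, delta 0.2, n = 50 gives 0.4/0.2 = 2.0 and type I error 0.51; n = 25 gives 0.4/0.283 = 1.41 and 0.28.

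| n per group | gap | delta 0.1 | delta 0.2 | delta 0.3 |
|---|---|---|---|---|
| 50 | 0 | 0.05 | 0.05 | 0.05 |
| 50 | 0.2 | 0.055 | 0.068 | 0.091 |
| 50 | 1 | 0.17 | 0.51 | 0.84 |
| 25 | 0.2 | 0.052 | 0.059 | 0.070 |
| 25 | 1 | 0.11 | 0.28 | 0.55 |

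**How large the gap may be if whole blocks alternate.**
- Control in the same block as its match: gap 0.
- Every control exactly one block later: p_n = 1 − p_r, so gap = 2p_r − 1. With rMDD entry spread evenly over blocks, its SD is 2 × sqrt(0.25/n) = 1/sqrt(n), which is 0.14 at 50 and 0.20 at 25. The mean is 0 for an even number of blocks and 1/17 = 0.06 in absolute value for 17 blocks. With 17 blocks an absolute gap of 0.2 or more occurs in about 24% of trials at 50 per group and 44% at 25. With an even number the binomial gives P(|2k − 50| ≥ 10) = 20% and P(|2k − 25| ≥ 5) = 42%. Averaged over this distribution at delta = 0.2, type I error is about 6% at either size; at delta = 0.1 it is about 5.3%.
- Lag varying uniformly over 0–1 to 0–4 blocks: SD 0.08 to 0.10 at 50 per group. Simple unstratified randomization has SD 0.10 and average type I error of about 5.5%.

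**How large it may be if sign-ups alternate one by one (50 per group).**
- Strict rMDD, ND, rMDD, ND entry throughout: absolute gap 1.
- Control following after a random lag with mean one rMDD inclusion: mean absolute shift 0.18, SD 0.15. Mean lag of five inclusions: 0.01, SD 0.12.
- Groups arriving in random sequence: mean 0, SD 0.10.

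**What a period term does.** In the within-person design with intervention, group × intervention and period, equal and opposite imbalance gives a correlation of size |gap| between the last two, and the variance of the aim 2 term is multiplied by 1/(1 − gap²). At gap 0.2 (60% against 40%) this is 1/0.96 = 1.04. At gap 1 the design has rank 2 of 3 and the two terms are the same contrast.

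**The case against.** The strongest reply is that the severe figures need an entry pattern the article does not describe. Complete aliasing requires person-by-person alternation and a constant lag of one sign-up for the whole trial. The sentence on three-week blocks points the other way, and so does group training: "participants receive one professional training session (2 h) in the intervention in groups of 2–8 people". Controls come through open advertising, must match on three characteristics and must pass screening, so lags will vary. This stands.

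A reader might infer that all rMDD participants start with one technique and all controls with the other. The article does not support that as an expectation. Nor do opposite orders within pairs imply opposite orders between groups: under block alternation with a one-block lag every pair is opposed, yet the group gap is close to 0 on average, because rMDD participants fall in both kinds of block. A reader might also infer that no model could rescue the test. That is true only at gap 1. Short of it, a period term removes a period effect common to both groups at small cost, and such a term may sit in an analysis plan that is not shown.

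It can also be said that the missing group stratum is inferred from a condensed article. The inference is fair in part, but the article does set out its rule specifically and limits its promise of balance to participants as a whole. A common period term, moreover, assumes the period effect is equal in rMDD and ND; balance within each group does not need that assumption.

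**Conclusion.** The concern holds in conditional form. The stated rule does not secure balance of order within rMDD and within ND, and the aim 2 contrast can carry a bias of 2 × (p_r − p_n) × delta. Under the block reading the expected harm is small: about 6% instead of 5% type I error at delta = 0.2 SD with a constant one-block lag, and less with varying lags. A single trial can still end with a gap of 0.2 or more, particularly in the 25-per-group physiology sample. The extreme of 51% (28% at 25 per group) belongs only to person-by-person alternation with strict paired entry. That the section's wording admits that reading is itself a reason to rewrite it. All sizes rest on an assumed delta and assumed lags; the article gives neither.

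**What to change.** In the Randomization section, state whether sign-ups or whole three-week blocks alternate. Allocate order separately within rMDD and within ND, so that about half of each group starts with each technique.

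For participants already enrolled, tabulate first technique by group, use any remaining starts to close a gap, include period × session in the aim 2 model, and report the table beside the aim 2 result. The article expected data collection to end in June 2024. If no starts remain, the table and the period term are still available, and the table will show whether the gap is small enough for the period term to suffice.

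Cost: a sentence or two in the allocation procedure, one model term and one small table. Some participants may wait one extra three-week block for the technique assigned to them. No additional participants or measurements are needed.

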### Procedure

After individuals have shown interest in participation in the study and are fully informed, they are asked to provide written informed consent. After providing informed consent, participants are screened for eligibility based on outcomes of the SCID-5, DART, IDS-SR30 and some sociodemographic background questions (see In- and exclusion criteria). When found eligible, they are asked to participate in the actual experiment that consists of five phases: a baseline individual characteristics measurement (T0) and four pre- and peri-intervention measurements periods (T1-T4; See Table 1, Figs. 2 and 3).

**Table 1 Tab1:** Overview of the MINDCOG assessments and their timing, where T0 refers to baseline characteristics before the start of the measurement period and T1-T4 the pre- and peri-intervention measurement sessions. More detailed information on the timing of the measurements assessed in T1-T4 can be found in Figs. 2 and 3

	**Screening**	**T0**	**T1**	**T2**	**T3**	**T4**
SCID-5 Interview	x					
IDS-SR30	x		x	x	x	x
DART	x					
AES		x				
BVAQ		x				
LEIDS-RR		x				
CTQ-SF		x				
DAS-A		x				
NEO-FFI		x				
ESM			x	x	x	x
Actigraphy			x	x	x	x
EEG			x	x	x	x
ECG/ICG			x	x	x	x
PTQ			x	x	x	x
RPA			x	x	x	x
ERQ			x	x	x	x
FFMQ			x	x	x	x
LARSS			x	x	x	x
PANAS			x	x	x	x
Expectation interview interventions			x			
Evaluation interview intervention				x		x

Abbreviations used in the table. *(SCID-5)* Structured Clinical Interview for DSM-5, *(IDS-SR30)* Inventory of Depressive Symptomatology - Self-Report, *(DART)* Dutch Adult Reading Test, *(AES)* Apathy Evaluation Scale, *(BVAQ)* Bermond-Vorst Alexithymia Questionnaire, *(LEIDS-RR)* Leiden Index of Depression Sensitivity-2nd revision, *(CTQ-SF)* Childhood Trauma Questionnaire-Short Form, *(DAS-A)* Dysfunctional Attitude Scale-form A, *(NEO-FFI)* NEO Five-Factor Inventory, *(ESM)* experience sampling method, *(EEG)* electroencephalogram, *(ECG)* electrocardiogram, *(ICG)* impedance cardiogram, *(PTQ)* Perseverative Thinking Questionnaire, *(RPA)* Responses on Positive Affect Scale, *(ERQ)* Emotion Regulation Questionnaire, *(FFMQ)* Five Facet Mindfulness Questionnaire, *(LARSS)* Leuven Adaptation of the Rumination on Sadness Scale, *(PANAS)* Positive and Negative Affect Schedule

**Fig. 2 Fig2:**
[figure not shown]
Overview of a pre-intervention measurement session (T1, T3)

**Fig. 3 Fig3:**
[figure not shown]
Overview of a peri-intervention measurement session (T2, T3)

#### Baseline individual characteristics (T0)

As baseline measurement (T0) self-report questionnaires are administered to measure individual characteristics that could serve as individual markers to predict treatment efficacy. Based on factors associated with the longitudinal course of depression, these include personality [44, 53], attitudes [21], depression sensitivity [54], childhood trauma [44], alexithymia [55], and apathy [56]. We administer the NEO Five-Factor Inventory (NEO-FFI) [57], Dysfunctional Attitude Scale-form A (DAS-A) [21], Leiden Index of Depression Sensitivity-2nd revision (LEIDS-RR) [58], Childhood Trauma Questionnaire-Short Form (CTQ-SF) [59], Bermond-Vorst Alexithymia Questionnaire (BVAQ) [60], and Apathy Evaluation Scale (AES) [56] and some questions about their expectations about the interventions. This takes approximately 65 min. Questionnaire data is collected and stored using REDCap.

#### Pre- and peri-intervention measurements procedure (T1-T4)

A few days before the start of the pre- and peri-intervention measurements, participants receive instructions about how to perform the measurements. The pre-and peri-intervention measurements include momentary ESM, the Sustained Attention to Response Task (SART), actigraphy, ICG/ECG measures, laboratory EEG measures, and questionnaires. The measurements are the same for each pre-and peri-intervention session.

##### ESM

Participants complete ESM questionnaires about sleep, feelings, thoughts, environment, and events using ESM via a mobile phone. In total, six ESM items about sleep are administered once per day and 24 ESM items are administered ten times per day for seven days in total. Filling out these questionnaires takes approximately five minutes. An overview of the ESM items can be found in Supplementary Materials 1. Data is collected and stored using RoQua, a highly protected system to manage and collect ESM data. Information on the dynamics and content of self-reported PC are extracted from the ESM data using the following variables: rumination, occurrence of off-task thinking, valence of thoughts, temporal orientation of thoughts, self-relatedness of thoughts, and stickiness of thoughts (i.e., how difficult it is to disengage from the thought).

##### SART

Participants perform a short version of the SART adapted from McVay and Kane [61], developed for use via a mobile application. The SART is a cognitive Go/No-Go task combining self-report measures of PC with task performance. The SART is performed twice-a-day for seven days and takes approximately five minutes to perform. Data is collected and stored using a protected server of the University of Groningen, the Netherlands. The task includes four blocks with four thought probe questions (asking about the content, valence, temporal orientation, and stickiness of the current thought) per block. Both self-reported PC (extracted from probe questions on the content, valence, temporal orientation and stickiness of the current thought) and task-performance (i.e., response times and accuracy) are extracted from the SART and used for further analyses.

##### Actigraphy

Actigraphy is measured with an epoch every 60 s for seven days using a MotionWatch 8 (CamNtech; www.camntech.com/motionwatch-8/). Data is stored on a shielded drive and pre-processed using the CamNtech MotionWare software. Sleep variables including total sleep time, sleep quality, and sleep onset latency are extracted from the data using the MotionWare software.

##### ECG/ICG

Participants are asked to wear an ambulatory cardiac monitoring system (VU-AMS; www.vu-ams.nl) [62, 63] for 24-h that allows us to measure ICG and ECG. In the peri-intervention measurement period, the VU-AMS device is worn on the last 24-h of the measurement period. Participants can apply the devices themselves using instructions or with remote help of the research team. The VU-AMS system contains seven electrodes, three ECG electrodes and four ICG electrodes. Data is sampled at a frequency of 1000 Hz and stored on a shielded drive. After data collection, the data is pre-processed using the VU-AMS software and matched with participants’ self-reported PC derived from the ESM data. An interval of 5-min before the time of the ESM beep in which participants reported PC is marked in the ECG to study the psychological correlates of self-reported PC.

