## Statistical analyses

### Study aim 1

To test whether psychological and psychophysiological indices of PC are differentially affected by fantasizing vs. mindfulness, we will examine within-subject changes in pre- and peri-intervention measurements in the dynamics and content of self-reported PC, HR and HRV during self-reported PC, and electrophysiological correlates of PC and compare those between the fantasizing and mindfulness condition. We will check whether the relationships are linear or nonlinear. If the relationships are linear, we will perform linear mixed effect models (LME). If the relationships are non-linear, we will perform generalized additive models (GAMs) [71].

To examine changes in the dynamics and content of self-reported PC after interventions, several variables of PC over time will be examined. Specifically, we will consider rumination, occurrence of off-task thinking, valence of thoughts, temporal orientation of thoughts, self-relatedness of thoughts, and stickiness of thoughts. If interventions differently affect these variables of PC, we expect to find an interaction effect between intervention (fantasizing or mindfulness), session (pre- or peri-intervention), and time (time of ESM beep). For example, we hypothesized that mindfulness increases the frequency of present thoughts (i.e., temporal orientation of thought) in contrast to fantasizing where we do not expect this. If this would be the case, an interaction effect between intervention, session, and time on the temporal orientation of thoughts would be found. After running the LMEs or GAMs, visualization of the data will be used to further study the dynamics of the different changes over time.

To examine within-subject changes in pre- and peri-intervention measurements on the physiological correlates of PC, we will examine changes in HR and HRV and EEG voltage during self-reported PC. If interventions differently affect these physiological correlates of PC, we expect to find an interaction effect between intervention (fantasizing or mindfulness), session (pre- or peri-intervention), and time (in minutes to milliseconds).

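### Ambulatory HR and HRV, primary outcomes in 25 per group, are modelled with no movement term although simultaneous actigraphy could supply one; the main cost is avoidable noise

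*Protocol article*

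**What the plan says.** The Outcome measures section lists HR and HRV during PC as primary outcomes for aims 1 and 2. The ECG/ICG section gives their source: "Participants are asked to wear an ambulatory cardiac monitoring system" for 24 hours per measurement period. On timing it adds: "In the peri-intervention measurement period, the VU-AMS device is worn on the last 24-h of the measurement period". On processing, "the data is pre-processed using the VU-AMS software and matched with participants’ self-reported PC derived from the ESM data". The window used is fixed there too: "An interval of 5-min before the time of the ESM beep in which participants reported PC is marked in the ECG".

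Statistical analyses, Study aim 1, describes the test for the physiological outcomes: "we expect to find an interaction effect between intervention (fantasizing or mindfulness), session (pre- or peri-intervention), and time (in minutes to milliseconds". Aim 2 adds group. The closing paragraph of that section adds random effects, with individual variability as the example.

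The Actigraphy section says "Actigraphy is measured with an epoch every 60 s for seven days", and then "Sleep variables including total sleep time, sleep quality, and sleep onset latency are extracted from the data". The outcome and analysis sections likewise use actigraphy only for sleep. Under COVID-19 related changes to the study design, ECG/ICG and actigraphy belong to the same phase, with 25 participants per group.

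**The concern.** The Background describes the cardiac signature of PC as raised HR with lowered HRV. Walking or cycling just before a beep moves both measures in the same direction. In a free-living five-minute window the two sources cannot be told apart unless movement is measured and used. A person-level random effect does not help, because movement varies between windows within a person.

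The article already accepts that outside influences on this signal need control: it excludes people taking beta blockers and other drugs that could affect the ECG or ICG. Movement gets no comparable step, although an actigraph on the same participants records it minute by minute. At stake are the precision of a primary outcome in the smaller physiological sample and, under some conditions, the meaning of a pre-to-peri change in HR or HRV.

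**Working it through.** **1. The article's own figure.** For HR it gives d = 0.96, two-tailed, 80% power, 19 per group. A two-sample t-test (noncentral t, alpha 0.05) gives n = 18.05, which rounds up to 19, so the figure reproduces. With the 25 per group planned, power at d = 0.96 is 91%. This arithmetic is sound and is not the problem.

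**2. Available data.** Beeps come ten times a day, so a 24-hour recording holds about ten windows, fewer once restricted to beeps with reported PC. Each five-minute window spans 5 × 60 s / 60 s = 5 actigraphy epochs.

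**3. Noise in a session mean.** All inputs here are assumptions: a share p = 0.2 to 0.4 of windows follows physical activity, active and inactive HR differ by 15 to 30 bpm, and n = 5 windows are usable.
- SD of the active share = √(p(1−p)/n): √(0.2 × 0.8/5) = 0.179; √(0.4 × 0.6/5) = 0.219.
- SD added to a session mean: 0.179 × 15 = 2.7 bpm to 0.219 × 30 = 6.6 bpm.
- SD added to a pre-to-peri difference: multiply by √2, giving 3.8 to 9.3 bpm.

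**4. Noise expressed as power.** Suppose unmodelled movement makes up a share s of HR variance, and suppose d = 0.96 is free of it (both assumed). The effective d is then 0.96 × √(1−s).

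| s | effective d | power, 25 per group | n per group for 80% |
|---|---|---|---|
| 0 | 0.960 | 91% | 19 |
| 0.1 | 0.911 | 88% | 20 |
| 0.2 | 0.859 | 85% | 23 |
| 0.3 | 0.803 | 80% | 26 |
| 0.4 | 0.744 | 73% | 30 |
| 0.5 | 0.679 | 65% | 36 |

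**5. Where bias can and cannot arise.** Let b be the HR change per unit of activity, and let a_M and a_F be the pre-to-peri activity shifts under mindfulness and fantasizing.
- Bias in the simple change: b × a_M or b × a_F.
- Bias in the intervention-by-session contrast: b × (a_M − a_F), which is zero if the shift is common.
- Bias in the group-by-session-by-intervention contrast: the difference between groups in b × (a_M − a_F), again zero if the shift is common to both interventions within each group.

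A common shift of 10 percentage points in the active share (assumed) moves the simple change by 0.10 × 15 = 1.5 bpm to 0.10 × 30 = 3 bpm, and moves the contrast by nothing.

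**6. False positives in the simple change only.** All inputs are assumed: activity–HR correlation ρ = 0.3 to 0.5, within-person HR correlation r = 0.5 to 0.7, activity shift 0.1 to 0.5 SD, paired test with n = 25. The standardised shift is ρ × shift / √(2(1−r)). For ρ = 0.5 and a 0.3 SD shift it is 0.15/1 = 0.15 at r = 0.5, and 0.15/√0.6 = 0.19 at r = 0.7. The rejection rates are 11% and 15%. Over the whole grid they run from 5% to 34%, against a nominal 5%.

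**The case against.** The strongest objection is that this is detail a condensed article leaves to a fuller document. The interaction sentence says what the authors expect to find and is not a full model specification. The random-effects sentence is openly illustrative, and the Actigraphy section does not rule out other uses of the counts. VU-AMS pre-processing might handle movement, and the ESM items on environment and events are in a supplement that is not shown. It stands that another document may cover the point. But the article does state the window, the processing, the model terms and the purpose of actigraphy, and movement appears in none of them. An analyst following it would leave movement in a primary outcome.

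A reader might go further and infer that movement will mimic a difference between mindfulness and fantasizing, for instance because training and practice are sedentary. The documents do not support that. The article calls the time, instructions and exercises of the two interventions comparable, so a shift caused by practising would be common to both and would cancel. The two-hour training precedes the daily exercises, while the peri recording covers the last 24 hours, so the training should lie outside it. The article does not say that participants practise seated. No recording day is stated in the text for the pre weeks, but Figs. 2 and 3, which carry the detailed timing, are not shown, so a difference in day cannot be claimed.

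Two further objections stand. Every bpm and variance figure above is assumed. And activity in the peri week is measured after the intervention has started, so adjusting for it changes what is estimated.

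**Conclusion.** The point holds as one about precision, with a conditional risk of bias. As described, the HR/HRV analysis leaves window-level movement in a primary outcome with 25 per group, while a concurrent measure of that movement goes unused for this purpose. The simple pre-to-peri change would be biased if activity differs by session. The intervention-by-session and group contrasts would be biased only if activity also differs by intervention or by group, for which the article offers no reason.

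The size cannot be derived from the article. The noise of 3.8 to 9.3 bpm on a difference, the fall in power to about 80% or 65%, and the 5% to 34% rejection range are illustrations under the stated assumptions. None of them shows that the 19 or 25 per group is miscalculated.

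**What to change.** In the ECG/ICG section, state that MotionWatch counts will be merged with each five-minute ECG window by time stamp. In Statistical analyses, for aims 1 and 2:

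- report the HR and HRV models both unadjusted and with the mean count over the window as a beep-level covariate;
- add a sensitivity analysis limited to windows below a low-activity threshold fixed before analysis;
- label the adjusted result as the change in HR or HRV at a given movement level, because peri-week activity is measured after the intervention starts.

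The cost is analysis wording and a merge of data already being collected. Windows without actigraphy drop out of the adjusted model, and the restricted analysis uses fewer windows. Counts also do not measure posture directly, so some non-PC variation will remain. If a fuller protocol or analysis plan already does this, a sentence pointing to it would be enough.
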